### 10.4.2 Analysis of the Primary Efficacy Endpoint(s)

The overall primary outcome is the change in body fat distribution, and the main specific endpoint is VAT.

### 10.4.3 Analysis of the Secondary Endpoint(s)

Secondary outcomes will be abdominal subcutaneous fat sub-depot and hepatic fat.

### 10.4.4 Safety Analyses

NA

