## 5.3 Strategies for Recruitment and Retention

Participants’ recruitment

The recruitment will be conducted among employees of the Nuclear Research Center, Dimona, Israel. The trial will be announced in the workplace and the potential participants will be contacted by the on-site clinic staff. The suitability of this setting is proven in several studies characterized by tight follow-up and/or interventions, which we performed in recent years^22^. Its advantages include an integral medical center, the possibility to perform most procedures within the workplace, and a secluded set of cafeterias amenable to dietary intervention.

Monitoring and Motivating Adherence

Adherence to the diet will be assessed by monitoring attendance of the nutritional sessions, and will be quantified via a self-administered validated electronic 127 item food-frequency questionnaires (FFQ) at baseline and after 6 and 18 months of intervention. By using electronic questionnaires, the completeness of the data was ensured by prompting the participants when a question was not answered or when an answer was not within a logical range. Adherence to the exercise intervention will be monitored frequently during the monthly group meetings and also quantified by calculating the METs/week using an electronic self-reported validated physical activity questionnaires at baseline and after 6 and 18 months. To motivate compliance, participants will be given a detailed individual report summarizing all their measurements after the completion of the trial. Participants who will not attend nutritional sessions or will decrease their gym attendance, as tracked online by the electronic gym entry monitor, will be contacted by telephone. Text messages will be sent to update participants and to motivate adherence to the diets on specific occasions (such as before and after holidays). Symptoms, adverse effects, quality of life, and medication usage will be measured at baseline and after 6 and 18 month, using validated electronic questionnaires^37, 42, 43^.

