### 7.3.7 Schedule of Events Table

**Table 3: Design of the intervention; the CENTRAL study**

| Year | 2012 | | | | 2013 | | | | | | | | | | | | 2014 | | |
| --- | --- | --- | --- | --- | --- | --- | --- | --- | --- | --- | --- | --- | --- | --- | --- | --- | --- | --- | --- |
| Month of intervention  Event | 0 | 1 | 2 | 3 | 4 | 5 | 6 | 7 | 8 | 9 | 10 | 11 | 12 | 13 | 14 | 15 | 16 | 17 | 18 |
| Dietary sessions |  | ++ | + | + | + | + | + | + | + | + | + | + | + | + | + | + | + | + | + |
| Physical activity intervention – gym membership provided |  |  |  |  |  |  |  | ++ | + | + | + | + | + | + | + | + | + | + | + |
| Whole body MRI | + |  |  |  |  |  | + |  |  |  |  |  |  |  |  |  |  |  | + |
| REE – Indirect calorimetry | + |  |  |  |  |  | + |  |  |  |  |  |  |  |  |  |  |  | + |
| Blood draw and urine samples (fasting) | + |  |  |  |  |  | + |  |  |  |  |  |  |  |  |  |  |  | + |
| Anthropometric measurements (WC, BP) | + |  |  |  |  |  | + |  |  |  |  |  |  |  |  |  |  |  | + |
| Weight measurement | + | + | + | + | + | + | + | + | + | + | + | + | + | + | + | + | + | + | + |
| Electronic questionnaires (FFQ, medical, symptoms, life-style, PA) | + |  |  |  |  |  | + |  |  |  |  |  |  |  |  |  |  |  | + |
| Physician follow-up (including reporting updates in drug usage, safety) |  |  |  |  |  |  | + |  |  |  |  |  | + |  |  |  |  |  | + |

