## 8.2 Classification of an Adverse Event

### 8.2.1 Severity of Event

The following guidelines will be used to describe severity:
• **Mild** – Events require minimal or no treatment and do not interfere with the participant’s daily
activities.
• **Moderate** – Events result in a low level of inconvenience or concern with the therapeutic
measures. Moderate events may cause some interference with functioning.
• **Severe** – Events interrupt a participant’s usual daily activity and may require systemic drug
therapy or other treatment. Severe events are usually potentially life-threatening or
incapacitating.

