### 8.2.2 Relationship to Study Agent

For all collected AEs, the clinician who examines and evaluates the participant will determine the AE’s
causality based on temporal relationship and his/her clinical judgment. The degree of certainty about
causality will be graded using the categories below.
• **Definitely Related** – There is clear evidence to suggest a causal relationship, and other possible
contributing factors can be ruled out. The clinical event, including an abnormal laboratory test
result, occurs in a plausible time relationship to drug administration and cannot be explained by
concurrent disease or other drugs or chemicals. The response to withdrawal of the drug
(dechallenge) should be clinically plausible. The event must be pharmacologically or
phenomenologically definitive, with use of a satisfactory rechallenge procedure if necessary.
• **Probably Related** – There is evidence to suggest a causal relationship, and the influence of other
factors is unlikely. The clinical event, including an abnormal laboratory test result, occurs within
a reasonable time after administration of the drug, is unlikely to be attributed to concurrent
disease or other drugs or chemicals, and follows a clinically reasonable response on withdrawal
(dechallenge). Rechallenge information is not required to fulfill this definition.
• **Possibly Related** – There is some evidence to suggest a causal relationship (e.g., the event
occurred within a reasonable time after administration of the trial medication). However, other
factors may have contributed to the event (e.g., the participant’s clinical condition, other
concomitant events). Although an AE may rate only as “possibly related” soon after discovery, it
can be flagged as requiring more information and later be upgraded to “probably related” or
“definitely related,” as appropriate.
• **Unlikely to be related** – A clinical event, including an abnormal laboratory test result, whose
temporal relationship to drug administration makes a causal relationship improbable (e.g., the
event did not occur within a reasonable time after administration of the trial medication) and in
which other drugs or chemicals or underlying disease provides plausible explanations (e.g., the
participant’s clinical condition, other concomitant treatments).
• **Not Related** – The AE is completely independent of study drug administration, and/or evidence

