## 8.3 Time Period and Frequency for Event Assessment and Follow-Up

The occurrence of an AE or SAE may come to the attention of study personnel during study visits and
interviews of a study participant presenting for medical care, or upon review by a study monitor.
All AEs including local and systemic reactions not meeting the criteria for SAEs will be captured on the
appropriate CRF. Information to be collected includes event description, time of onset, clinician’s
assessment of severity, relationship to study product (assessed only by those with the training and
authority to make a diagnosis), and time of resolution/stabilization of the event. All AEs occurring while
on study must be documented appropriately regardless of relationship. All AEs will be followed to
adequate resolution.
Any medical condition that is present at the time that the participant is screened will be considered as
baseline and not reported as an AE. However, if the study participant’s condition deteriorates at any
time during the study, it will be recorded as an AE.
Changes in the severity of an AE will be documented to allow an assessment of the duration of the event
at each level of severity to be performed. AEs characterized as intermittent require documentation of
onset and duration of each episode.
The PI will record all reportable events with start dates occurring any time after informed consent is
obtained until 7 (for non-serious AEs) or 30 days (for SAEs) after the last day of study participation. At
each study visit, the investigator will inquire about the occurrence of AE/SAEs since the last visit. Events
will be followed for outcome information until resolution or stabilization.

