# 14 DATA HANDLING AND RECORD KEEPING

## 14.1 Data Collection and Management Responsibilities

Data collection is the responsibility of the clinical trial staff at the site under the supervision of the site
PI. The investigator is responsible for ensuring the accuracy, completeness, legibility, and timeliness of
the data reported.
All source documents should be completed in a neat, legible manner to ensure accurate interpretation
of data. When making changes or corrections, cross out the original entry with a single line, and initial and date the change. DO NOT ERASE, OVERWRITE, OR USE CORRECTION FLUID OR TAPE ON THE ORIGINAL.

Copies of the electronic CRF (eCRF) will be provided for use as source documents and maintained for
recording data for each participant enrolled in the study. Data reported in the eCRF derived from source
documents should be consistent with the source documents or the discrepancies should be explained
and captured in a progress note and maintained in the participant’s official electronic study record.
Clinical data (including AEs, concomitant medications, and expected adverse reactions data) and clinical
laboratory data will be entered into the designated data storage system, which will include password protection and internal quality checks, such as automatic range checks, to identify data that appear inconsistent, incomplete, or inaccurate. Clinical data will be entered directly from the source documents.

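### Adverse events are graded and recorded but the safety analysis is declared not applicable, and no dated post-baseline enquiry falls before month 6

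*Protocol*

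**What the plan says.** **Collection and grading.** Section 8.2.1 sets three severity grades ("The following guidelines will be used to describe severity"). Section 8.2.2 says that "The degree of certainty about" causality is graded, in five categories, for all collected AEs. Section 8.3 has all AEs documented whether or not they are judged related, including time of onset, from consent until 7 days (non-serious) or 30 days (serious) after participation ends. Section 14.1 sends them to the database: "Clinical data (including AEs, concomitant medications, and expected adverse reactions data) and clinical" laboratory data are entered in the data storage system.

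**Analysis.** Under "10.4.4 Safety Analyses" the protocol writes NA and nothing else.

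**Timing.** Three routes are described:
- Section 5.3, by questionnaire: "Symptoms, adverse effects, quality of life, and medication usage will be measured at baseline and after 6 and 18 month". Table 3 (section 7.3.7) carries a matching electronic questionnaire row, which includes symptoms, at months 0, 6 and 18.
- Table 3, by physician: "Physician follow-up (including reporting updates in drug usage, safety"), marked at months 6, 12 and 18.
- Section 8.3, by the investigator: at "each study visit, the investigator will inquire about the occurrence of AE/SAEs since the last visit". The protocol does not define a study visit. Table 3 shows weighing every month and regular dietary sessions but does not say whether either counts.

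**The concern.** Collecting and grading events and then declaring their analysis not applicable is an inconsistency within the protocol. The Rationale (section 2.2) says the results are meant to inform lifestyle strategies for public health. Section 2.3.1 says that, to the investigators' knowledge, no risk is expected; the collected AEs are the data that would test that statement. A plan that leaves them unanalysed can report benefit by group but not harm by group.

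The timing matters because a table is only as good as the capture behind it. The strictest dietary phase is the first two months. If weighings and diet sessions are not study visits, nobody is scheduled to ask about AEs until month 6.

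**Working it through.** The protocol states no figure for safety, so there is none to reproduce. The check is a comparison of sections plus three short calculations for context.

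**1. Is NA an entry or an empty template field?** Within section 10.4, the headings 10.4.7.1, 10.4.7.2, 10.4.9, 10.4.10 and 10.4.11 are blank, whereas 10.4.4 is filled in with NA. Nothing elsewhere supplies a harms comparison: study halting rules (8.5) and interim analyses (10.4.7) are also NA, and Safety Oversight (8.6) has no text of its own.

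**2. Dated AE contacts.**
- Questionnaire: {0, 6, 18}. Physician: {6, 12, 18}.
- Combined: {0, 6, 12, 18}. The longest scheduled gap is 6 months.
- First dated post-baseline contact: month 6. Induction ends at month 2, so the enquiry comes 6 − 2 = 4 months later.
- Weighing: every month from 0 to 18. If it counts as a study visit, there are five further contacts (months 1 to 5) before month 6 and the longest gap falls to 1 month.

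The undefined term in 8.3 therefore decides whether early enquiry happens at all.

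**3. Do the routes differ by arm?** No. All three are written for every participant, and section 6.1 designs diet-session intensity to be equal between the diets. What differs from month 7 is contact outside these routes: the exercise groups are prescribed three gym sessions a week and a monthly workshop (6.1). Over 12 months that is at most 3 × 52 = 156 sessions and 12 workshops.

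**4. What unequal capture could do (assumed rates; the protocol gives none).** Apparent difference = true rate × (capture with exercise − capture without).

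| True AE rate, both groups | Capture 90% v 75% | Capture 90% v 60% | Equal capture |
|---|---|---|---|
| 10% | 1.5 points | 3 points | 0 |
| 20% | 3 points | 6 points | 0 |
| 30% | 4.5 points | 9 points | 0 |

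This shows the mechanism; it does not show that it operates here.

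**5. How precise a harms table would be.** With 125 v 125 (section 10.6.1), two-sided alpha 0.05, 80% power and a normal approximation for two proportions, the detectable contrasts at assumed reference rates are 5% v 15.8%, 10% v 23.2% and 20% v 35.9%. If no event of a given type is seen, the one-sided 95% upper bound is 1 − 0.05^(1/n): 2.4% for n = 125 and 4.7% for n = 62 (250/4 = 62.5 per group). These figures describe the limits of the table. They do not measure the defect, since they are the same whether or not the analysis is declared NA.

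**The case against.** **NA may be template filler.** Section 8.4.3 also reads NA although 8.1.3 adopts a definition of unanticipated problems, and the layout of AE tables is commonly left to a statistical analysis plan, which is not shown here. This weakens any claim of deliberate intent. It does not remove the inconsistency: an analysis plan that followed this protocol would have no harms table, and one that included such a table would contradict it.

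**The collection times do not conflict.** A reader might infer from 5.3, Table 3 and 8.3 that the protocol gives three contradictory AE schedules. It does not. Table 3 contains both the physician row and a questionnaire row that matches 5.3, so these are complementary instruments, and 8.3 adds a general duty to enquire. What stands is the undefined study visit and the absence of any dated contact between baseline and month 6.

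**Other routes exist early on.** Section 8.3 also picks up events when a participant presents for medical care, section 4.1 describes continuous monitoring by the study nurse, and 8.4.1 names the head of the workplace medical centre among those notified. These reduce the early gap, but they depend on the participant coming forward and are not a uniform question put to everyone.

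**Bias against the exercise groups is conjecture.** No section makes gym staff AE collectors. The 156 sessions are a planned maximum, and section 4.1, which has participants guided at first and then followed by gym card, leaves it open whether every session is supervised. This objection stands: unequal capture is plausible, not established.

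**Conclusion.** The point holds in a limited form. AEs are to be graded, documented and entered in the database, while the safety analysis is declared not applicable, so as written there is no harms comparison by randomised group. Separately, the AE enquiry rule rests on an undefined visit, and the dated contacts contain none between baseline and month 6, so early events could be missed.

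Two stronger readings are tempting and are not supported:
- That harms cannot be compared fairly between arms. No schedule differs by arm and diet contact is designed to be equal, so loose timing makes capture unclear and possibly incomplete in all groups rather than biased. For exercise v no exercise, gym contact and open-label allocation could make spontaneous reporting unequal from month 7, but its existence and size rest entirely on assumed capture rates.
- That recall runs to 12 months. That is true of the questionnaire taken alone; with physician follow-up included, the longest scheduled gap is 6 months.

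The defect is one of safety planning and reporting. It does not touch the analysis of visceral fat. It merits correction because the data are already to be collected and the remedy is cheap.

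**What to change.** 1. In section 10.4.4, replace NA with a descriptive table of the number of participants with any AE, any related AE, any serious AE and any AE leading to withdrawal: by diet for months 0-6, among all randomised, and by the four randomised groups for months 6-18, among those re-randomised. Time of onset is already collected under 8.3, so events can be assigned to the right period.
2. In section 8.3, state that the monthly weighing already in Table 3 counts as a study visit at which the same AE question is asked of every participant in all arms. The questionnaire and physician contacts can stay as they are.

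**Cost.** One table, one question at an existing contact and modest extra AE data entry. The comparison will remain descriptive and imprecise at this sample size. A common question equalises structured enquiry but not what participants volunteer at the gym, so the exercise comparison should still be read with that in mind.

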### 10.4.5 Adherence and Retention Analyses

Adherence to the diet and exercise will be assesse monthly by monitoring attendance to the sessions, and also by questionnaires (FFQ and PA) at baseline and after 6 and 18 months.

### 10.4.6 Baseline Descriptive Statistics

At baseline we will preforme ANOVA and t-test to demonestrat diffrences between the study groups

### 10.4.7 Planned Interim Analyses

NA

#### 10.4.7.1 Safety Review

#### 10.4.7.2 Efficacy Review

#### 10.4.8 Additional Sub-Group Analyses

Sensitivity analyses within the stratum of men only will be test

### 10.4.9 Multiple Comparison/Multiplicity

### 10.4.10 Tabulation of Individual Response Data

### 10.4.11 Exploratory Analyses

## 10.5 Sample Size

Sample size was estimated based on findings from a previous 14-week intervention study, in which 33 postmenopausal obese women (57 yr, 92 kg, 36% body fat) were randomized to one of three interventions: diet alone, exercise alone, and diet and exercise group. We observed a significant relative change in VAT of 12.8% (P<0.05). Thus, the minimum detectable effect after 18 months for the primary VAT between the intervention groups was estimated as 3.57cm^2^, and for an alpha=5% and power=80%, 250 participants were required (calculated using Winpepi software).

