# 2 INTRODUCTION: BACKGROUND INFORMATION AND SCIENTIFIC RATIONALE

## 2.1 Background Information

**Introduction:**

*Abdominal obesity signifies fat distribution associated with increased risk for obesity-related co-morbidity*. Obesity – the conversion of chronic surplus in calories into excessive accumulation of adipose tissue – is becoming a major threat to human health in the twenty-first century^1^. The association between obesity and cardio-metabolic risk does not follow a simple linear relationship^2^; Whereas some individuals have largely increased body mass index (BMI) with minimal health consequence^3^, others display a complex of metabolic, endocrine and vascular abnormalities with even mild increase in BMI beyond the accepted upper limit of 25 kg/m^2^. The reasons for this variability in the toll of excessive adipose tissue accumulation on health are largely unknown. Yet, *the anatomical locations in which adipose tissue accumulates* may be a significant factor^4,5^; As noted decades ago, fat accumulation in the lower part of the body, also called gynoid obesity, is rather benign and may even be protective against obesity-related morbidity. In contrast, upper body fat accumulation, particularly in the abdominal region, strongly associates with increased risk for diabetes and cardiovascular disease.  *Abdominal fat consists of several distinct fat depots*. SAT, represents fat accumulation outside the abdominal cavity ^6^. Within the abdominal cavity fat accumulates mainly around the internal organs- VAT and in the omentum. Among moderately obese healthy men large inter individual differences are observed for total adipose tissue (AT) volume (6.9-59.3 liters), SAT (6.3-49.8 liters), and VAT (0.5-8.5 liters)^7^. VAT represented 18.3% of the total AT. A distinct retroperitoneal fat also exists. Multiple studies now demonstrate that different fat depots are in fact quite distinct in their metabolic and endocrine functions (^2,5^ and **Table 1**). Firstly, while the venous drainage of subcutaneous and retroperitoneal fat is to the systemic circulation, visceral and omental fat drain into the portal system, thus, communicating directly with the liver by virtue of secreted products. Yet in addition, gene array analyses demonstrate significant differences between the fat depots in multiple developmental genes, suggesting intrinsic, genetically-encoded heterogeneity between fat tissues ^8^. These translate into important functional differences, including relatively increased sensitivity of intra-abdominal fat to lipolytic stimuli, and differential secretion of various fat-derived "adipokines". Rodent models suggest that in response to chronic excess in calories, intra-abdominal fat mainly responds by hypertrophy (and large adipocytes are thought to be more insulin resistant and "dysfunctional"), whereas subcutaneous fat tends to respond by hyperplasia^9^. In established obesity the cellular composition of adipose tissue in different depots is also distinct, with macrophages infiltrating to a larger degree the intra-abdominal versus the SAT^10, 11^. *Intriguingly, although increased waist circumference correlates with increased intra-abdominal fat mass, it may in fact represent predominant expansion of different depots in the abdomen.* In fact, some individuals exhibit a predominant accumulation of abdominal subcutaneous or of intra-abdominal fat^11, 12^, potentially resulting in comparable waist circumference. The distinction between persons with "predominant intra-abdominal (IA) adiposity" versus those with "predominant subcutaneous (SC) adiposity" relies on determining the SC/IA ratio based on imaging approaches^11^, as will be described in Section c.2. Intriguingly, when measured, it is the intra-abdominal fat mass which best correlated with glucose intolerance, insulin resistance, low HDL, high TG and hypertension^13, 14^. *Visceral fat is therefore suggested as a unique, pathogenic fat depot^15, 16^*. Yet, a *causative role* for intra-abdominal fat in the co-morbidity of obesity is not well established, and is still debated.

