*There are several comparable dietary strategies to induce weight loss, but their effect on specific abdominal fat depots is unclear*. The effectiveness for weight loss^18-20^, and superiority for cardiovascular benefits^21^ of low-fat diets components is debated. Recently we completed a 2-years intensive workplace-based Dietary Intervention Randomized Controlled Trial (DIRECT)^22^ among 322 participants, who were assigned to three intervention arms - Low-fat diet, Mediterranean diet (MED), and low-carbohydrate (low-carb) diet. Adherence was 95% at 1 year and 85% at 2 years. The results [see details in the preliminary (c.3.) and figures sections] suggest that whereas the low-carb diet was superior in improving lipid profile and weight loss, the Med diet (high in mono-unsaturated fat-MUFA) provided the largest decrease in circulating insulin and glucose levels. All three arms induced similar dynamics in weight, revealing a weight-loss phase (0-6 months) and a subsequent regain-plateau (6-24 months) phase (N Engl J Med 2008). Specific loss of VAT mass has mostly been shown in response to exercise training^23^. Gene expression of adiponectin in VAT and SAT is modified by physical training^24^. However, dietary strategy to preferentially promote loss of VAT is unknown. Several lines of evidence suggest differential roles of macronutrients in the *accumulation* of intra-abdominal (visceral) adipose tissue. VAT cells have a two-fold higher glucose uptake rate and de-novo lipogenesis capacity compared with SAT cells^25^. Glucose-stimulated insulin secretion may also have preferential effects on VAT, as insulin-stimulated glucose uptake and lipogenesis, and the stimulation of the expression of 11-β-HSD1 with resulting increase in active cortisol, are more evident in VAT, enhancing VAT accumulation^26^. Feeding rats with a high sucrose diet increase not only muscle insulin resistance, but also VAT mass^27^, at least partly by promoting cell hypertrophy^28,29^. In a 4-week intervention study among 22 human obese subjects, a larger decrease in VAT measured by computed tomography was observed in the low-carbohydrate diet group compared to the high-carbohydrate diet group^30^. *It is therefore possible that reducing carbohydrate load may preferentially decrease VAT accumulation*. In contrast, dietary fat explained only two percent of the variance in general adiposity, and was unrelated to VAT mass when measured in cross-sectional studies^31^. A recent study on 42 monkeys compared diets containing either monounsaturated fatty acids or an equivalent diet containing trans-fats for 6 years^32^. It was shown that trans-fat-fed monkeys gained significantly more weight, associated with increased intra-abdominal fat deposition and insulin resistance, compared to monkeys fed diet rich in monounsaturated fatty acids. In humans, in a cross-sectional study among 334 female twins there was no relationship between total dietary fat composition and adiposity^33^. However, in women at low genetic risk of abdominal obesity, subjects with higher polyunsaturated fat intakes had about 50% less central abdominal fat than subjects with lowest intake. Thus, a suggested preventive strategy for VAT accumulation may include limiting dietary carbohydrates and apparently, increasing monounsaturated fats^34^. Therefore, some evidence suggests that VAT accumulation may be linked to carbohydrate load in the diet, whereas the fat load (accept for trans-fatty acids) plays a minor, or even protective role (in the case of monounsaturated fat). *However, large-scale intervention trials assessing whether limiting carbohydrates and increasing monounsaturated fat can assist in inducing VAT loss beyond the weight loss induced by conventional hypocaloric diet are required to establish the relationship between dietary macronutrients composition, intraabdominal adiposity and insulin resistance.*

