## 10.4 Description of Statistical Methods

### 10.4.1 General Approach

Results will be presented as means ± SD unless otherwise stated. Analysis of variance with a covariance (ANCOVA) test will be used in order to assess adherence to the interventions (attendance of the group sessions) and differences in changes nutrient intakes between the diet strategies. General linear models will be used to compare the trajectories of body weight and WC across the four intervention groups. We will use multivariate two-way ANCOVA and compare type of diet and physical activity as fixed factors (2*2 factorial design) to test changes in specific fat depots, using mean of differences and 95% CIs for each intervention group over time. Optional interactions between diet and exercise will be assessed by the ANCOVA models. To assess the effect of the combination of diet and PA, general linear models will be used with LFPA– as the reference. All models will be adjusted for age, sex, baseline abdominal obesity and 18-month weight change. Changes in the various fat depots and deposits will be evaluated both as absolute and relative changes. The association between changes in abdominal fat and intra-hepatic fat, and changes in levels of blood biomarkers will be tested using multivariate linear regression models, adjusted for age, sex, weight change, intervention group and baseline abdominal fat status (for the abdominal fat models) or baseline intra-hepatic fat (for the hepatic model). Homeostasis-model-assessment-of insulin-resistance (HOMA-IR) will be calculated according to the following equation: insulin (U/ml)×fasting glucose(mmol/liter) ÷22.5. Statistical analysis will be performed with IBM SPSS (version 23). All *P*-values will be two-sided, and *P*<0.05 will be considered statistically significant.

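### Section 10.5 gives neither the SD nor the contrast behind its 250 participants, and its 80% power leaves no room for lost VAT data

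*Protocol*

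**What the plan says.** Protocol section 10.5 takes its starting point from outside the trial: "Sample size was estimated based on findings from a previous 14-week intervention study, in which 33 postmenopausal obese women" were split between diet, exercise, and both. From that study it reports: "We observed a significant relative change in VAT of 12.8% (P<0.05"). The next sentence opens with *Thus* and says that "the minimum detectable effect after 18 months for the primary VAT between the intervention groups was estimated as 3.57cm^2". It concludes that "for an alpha=5% and power=80%, 250 participants were required (calculated using Winpepi software"). No SD, baseline VAT, named contrast or loss rate appears.

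Other sections bear on this:

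- Section 10.6.1 assigns 125 participants to each diet. The Protocol Summary then splits them into four equal groups after 6 months.
- Section 10.4.1 plans a 2×2 factorial ANCOVA with optional diet-by-exercise interactions. For the combination of diet and exercise, "general linear models will be used with LFPA" without added physical activity (LF PA–) as the reference. Tests are two-sided.
- Section 5.4.2 does not replace participants who leave.
- Section 10.3 expects some missing 18-month fat data and fills them by multiple imputation from age, gender, baseline weight or BMI, and waist at the end of the intervention.

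**The concern.** VAT is the main endpoint, and section 10.5 is the only justification for the size of the trial. A reader cannot get from the stated inputs to 250, because the quantity that decides the answer, the SD of VAT change, is absent. The contrast is also open: the phrase about intervention groups fits two diets of 125 or any two of four groups of about 62.

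The number required equals the number enrolled, so the stated power assumes that every participant yields 18-month VAT information. Sections 5.4.2 and 10.3 show that the plan does not expect this. At stake is how a null result is read. Without a statement of what was sized, a non-significant comparison with LF PA–, or a non-significant interaction, could be taken as an 80%-powered null.

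**Working it through.** **Inputs.** Difference d = 3.57 cm², alpha 0.05, power 0.80 and N = 250 (section 10.5); two-sided testing (section 10.4.1); 125 per diet (section 10.6.1); four equal groups, 250/4 = 62.5 each (Protocol Summary). The SD is not given and has to be solved for. All results use the normal approximation.

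**1. Reproducing 250.** With z-values 1.960 + 0.8416 = 2.8016 and n per group, SD = d / (2.8016 × √(2/n)).

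- Two diets, n = 125: 3.57 / (2.8016 × 0.12649) = 10.07 cm² (10.03 with the t distribution).
- Two of four groups, n = 62.5: 3.57 / (2.8016 × 0.17889) = 7.12 cm².

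The total depends strongly on this missing value. For two arms it is 62 at SD 5, 248 at SD 10 and 556 at SD 15. These SDs only illustrate the sensitivity; they are not estimates. So 250 can be made to fit, but it cannot be checked.

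**2. Loss of VAT data.** With retention r, the standardized difference shrinks from 2.8016 to 2.8016 × √r. Power is Φ(2.8016√r − 1.960), and the difference detectable at 80% is 3.57/√r. Neither depends on which of the two SDs was used, so the result applies to whichever contrast was sized.

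| Retention (assumed) | Power for 3.57 cm² | Detectable at 80% |
|---|---|---|
| 100% | 80% | 3.57 cm² |
| 95% | 78% | 3.66 cm² |
| 90% | 76% | 3.76 cm² |
| 85% | 73% | 3.87 cm² |

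The range is an assumption. The only related figures are in section 2.1, for an earlier workplace diet trial: "Adherence was 95% at 1 year and 85% at 2 years". Those are adherence rates, not the availability of an 18-month MRI in this trial.

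**3. The other contrasts, with all 250 contributing.**

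- One group against LF PA–: standard error SD × √(2/62.5). At SD 10.07 this is 1.801, so power is Φ(3.57/1.801 − 1.960) = 51%, and the detectable difference is 2.8016 × 1.801 = 5.05 cm². At SD 7.12 power is 80% by construction.
- Diet or exercise main effect, about 125 v 125: 80% at SD 10.07 and 98% at SD 7.12.
- Interaction (difference of differences) of 3.57 cm²: standard error SD × √(4/62.5). At SD 10.07 this is 2.547 and power is 29%; at SD 7.12 it is 1.801 and power is 51%.

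**The case against.** The best defence has four parts.

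**The four-group comparisons may have been sized.** A reader might infer that the plan fails to give 80% for comparisons with LF PA–. The document does not establish that. If 250 was sized on pairs of the four groups (SD 7.12), those comparisons have 80% and the main effects 98%, or 95.5% at 85% retention. The 51% figure is conditional on sizing by diet. That is the more natural reading, since 125 is attached to each diet, but it is not stated. For interactions, which section 10.4.1 calls optional, the protocol never claims 80%. The figures show what should be disclosed, not a broken promise.

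**Nothing shows that 3.57 cm² is wrong.** It is tempting to divide 3.57 by 0.128, get 27.9 cm², and call that an implausibly low baseline beside the quoted "SAT (6.3-49.8 liters), and VAT (0.5-8.5 liters") for moderately obese men. This does not stand. The text does not say that 3.57 is 12.8% of a mean. Turning litres into an area needs an assumed abdominal length, whereas section 7.1.1 averages three lumbar slices. Entry also admits people on lipids alone, and women. The document gives no VAT area to contradict the figure.

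**The true SD is unknown in both directions.** Much larger SDs would cut even the main-effect power, but no such value has support in the document. Covariate adjustment could also lower the residual SD by an amount not given.

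**Imputation keeps everyone in the analysis.** That is true, but it recovers information only as far as its predictors are available and informative. End-of-intervention waist is measured at the 18-month visit, and section 7.3.5 has no early termination visit. Someone who has left will usually lack it too.

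What remains is the missing SD, the missing contrast, the unexplained step from 12.8% to 3.57 cm², and the absence of any allowance for loss. Since section 10.5 states the calculation as complete, these are faults in what it says, not detail left to an analysis plan.

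**Conclusion.** The point holds in this form. The 250 cannot be reproduced from section 10.5, and the stated 80% is not delivered once VAT data are lost. On either sizing, the contrast that was sized has about 78%, 76% or 73% power at 95%, 90% or 85% retention, before whatever imputation restores. The shortfall is modest, but it affects the primary endpoint.

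Conditional on sizing by diet, comparisons with LF PA– have about 51% power for 3.57 cm². On neither sizing does an interaction of that size reach 80% (29% or 51%). These results rest on the back-solved SDs, two-sided tests, equal groups and the assumed retention range. They do not show that the main effects are underpowered with full data, or that 3.57 cm² contains an error of unit or scale.

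**What to change.** Rewrite section 10.5 to give:

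- the SD of 18-month VAT change (or the residual SD, if ANCOVA was assumed) and its source;
- how 3.57 cm² was obtained from the 12.8% figure, including whether that was a change within a group or a difference between groups;
- the contrast that was sized, with its group sizes;
- the expected loss of 18-month VAT data, and the power or detectable difference at that retention;
- which planned contrasts are not powered at 80%: the interaction and, if the two diets were sized, the comparisons against LF PA–.

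The cost is one paragraph. No participants need be added and the design does not change. The stated figures become slightly less favourable.
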